# SYNOPSIS

| **Study Title** | **P**rimary **C**are **Shop**ping Intervention for Cardiovascular Disease Prevention | |
| --- | --- | --- |
| **Internal ref. no. / short title** | PC-SHOP | |
| **Study Design** | Individually randomised, 3 arm parallel group study | |
| **Study Participants** | Adults ≥18 years of age with high LDL-cholesterol who are primarily responsible for household shopping and shop at Tesco at least once a week using Tesco’s storecard. | |
| **Planned Sample Size** | 112 total, 48 participants in each intervention group and 16 in the control group | |
| **Planned Study Period** | 24 months  Recruitment of practices will take 2 months, recruitment of participants will take around 10 months and each participant will be followed up for 3 months. The qualitative study will take approximately 9 months to complete. | |
|  | **Objectives** | **Outcome Measures** |
| **Primary** | To test a behavioural intervention aiming to promote a reduction in saturated fat (SFA) intake through brief advice from a qualified health professional alone or in combination with feedback on food purchasing behaviours against usual care. | Change in mean %SFA intake, measured using 2 x 24h dietary recalls twice (once at baseline and once 3 months later), using a validated web based questionnaire |
| **Secondary** | 1. Change in SFA content of food purchases  2. Biochemical markers of CVD risk  3. Change in food intake patterns | 1. 3-month changes in mean %SFA from total purchases; proportion of food items with low SFA (e.g. products with ≤1.5 grams of SFA per 100 grams of the product) between baseline and 3 months.  2. Changes in mean LDL-cholesterol, HDL-cholesterol, total cholesterol, non-HDL cholesterol, total cholesterol/HDL ratio and triglycerides between baseline and 3 months.  3. Changes in the intake of high SFA food groups between baseline and 3 months. |
| **Non-efficacy outcomes** | 1. Change in other components of diet  2. Other nutrient content of food purchases  3. Blood pressure  4. Body weight  5. Feasibility of the intervention and process measures  6. Qualitative sub-study | 1. 3-month changes in mean total energy intake, total fat, total sugars, fibre and salt between baseline and 3 months.  2. 3-month changes in mean energy density, total fat, sugar, fibre and salt from total purchases; mean total cost of the shopping basket (£) between baseline and 3 months.  3. Changes in mean systolic and diastolic blood pressure between baseline and 3 months.  4. Changes (absolute (kg) and relative (%)) in body weight between baseline and 3 months.  5. Feasibility of the intervention and process measures:  - Willingness of participants to take part in the study and be randomised to measure recruitment rates.  - Follow-up rates to measure programme attendance and retention.  - Acceptability of the intervention and other process measures.  6. Themes and sub-themes pertaining to the participants’ (i) knowledge, (ii) perceived barriers, facilitators and actions, (iii) contextual influences, and (iii) value of the healthcare advice provided. |

# ABBREVIATIONS

| AE | Adverse Event |
| --- | --- |
| BHF | British Heart Foundation |
| CI | Chief Investigator |
| CRF | Case Report Form |
| CTRG | Clinical Trials & Research Governance, University of Oxford |
| CVD | Cardiovascular Disease |
| GCP | Good Clinical Practice |
| GP | General Practitioner |
| HDL | High density lipoprotein cholesterol |
| HP | Health Professional |
| ICF | Informed Consent Form |
| LDL | Low density lipoprotein cholesterol |
| NHS | National Health Service |
| NICE | National Institute for Health and Care Excellence |
| NRES | National Research Ethics Service |
| PIL | Participant/ Patient Information Leaflet |
| R&D | NHS Trust R&D Department |
| REC | Research Ethics Committee |
| SFA | Saturated Fat |
| SOP | Standard Operating Procedure |

# BACKGROUND AND RATIONALE

Poor diet is a major contributor to cardiovascular disease (CVD). Saturated fat (SFA) increases the production of low-density lipoprotein cholesterol (LDL-C) and decreases its clearance from the body through suppression of the LDL receptor activity^1^. Meta-analyses of RCTs in which SFA has been replaced by unsaturated fats have estimated reductions of 10 to 17% in CVD events^2 3^, with particular improvements in vascular function produced by increases in monounsaturated fat^4^. However, progress in reducing SFA through public education programmes is slow, and SFA intake in the UK (13.5% energy) remains more than a third higher than the recommended value of <10% energy.

To identify effective interventions for LDL reduction through dietary improvements, we searched the Cochrane Database of Systematic Reviews, MEDLINE and the ISRCTN registry for ongoing studies and systematic reviews. The most recent systematic review and meta-analysis was published by the Cochrane Collaboration group in June 2015 and found that interventions to reduce SFA intake compared to usual diets resulted in a significant reduction in LDL cholesterol of 0.19 mmol/L [-0.33,-0.05] and 17% reduction in CVD risk^3^. The authors concluded that lifestyle advice should be given to those at risk of CVD and to lower risk population groups to achieve a meaningful reduction in saturated fat intake, which is consistent with the recommendations from NICE for CVD prevention^5^. However, while the evidence is clear about what should be done, it is far less clear that we have practical means of achieving these dietary changes in routine clinical practice.

Previous research has established that it is possible to achieve lower SFA intake through providing appropriate food stuffs in place of higher SFA products, in combination with intensive and tailored counselling^6 7^. However, the success of dietary advice alone to reduce SFA has been limited and has only been achieved with specialist staff and high intensity behavioural support^8 9^. It is increasingly recognised that the health system needs a mechanism to support a large number of people classified as at increased CVD risk. A recent small trial of dietary counselling in a primary care setting has shown a short-term beneficial effect on blood cholesterol^10^ but as yet there is no effective intervention that is sufficiently scalable and practical for routine delivery in primary care settings, or at population level.

Food purchasing is a key antecedent of food consumption and improving the nutritional quality of food purchases presents a clear opportunity to intervene. Supermarkets account for 71% of the weekly expenditure on food and drinks, including a large proportion of foods that are major sources of SFA in the diet such as meat, dairy, ready meals, cakes and biscuits^11^. Individual-level interventions targeting the nutritional quality of the grocery shopping could improve diet quality, especially among those motivated to change. However, previous evidence suggests that information provision alone might not be sufficient for sustained dietary change, and other behavioural strategies may be needed^12^.

Systematic reviews have identified effective intervention components for individual dietary change, including providing tailored dietary advice, information, self-monitoring and personalised feedback^13 14^. In-store education provision at the point of purchase has been shown to improve the nutritional quality of food purchases, and increase fruit and vegetable purchases^15^, and a previous intervention using an online supermarket showed a 10% reduction in SFA from food purchases by recommending lower SFA options at the point of purchase^16^. New technological advances within the food industry allowing the tracking of food purchases, including their nutritional content, offer the potential to deliver personalised nutrition interventions to reduce SFA intake. Here we plan to develop a programme to provide regular personalised feedback on the saturated fat content of food purchases, together with suggested alternatives with less saturated fat. To do so, we will establish a partnership with Tesco, the largest UK supermarket. Using a well-established storecard system, the store can track food purchases which can be linked to a nutritional database to calculate the nutritional content of the basket and, with further development, identify substitutes containing less saturated fat. The study will be run by the University of Oxford.  With participant consent, Tesco stores will provide data to the study team in order to enable the study to run. Tesco will not receive any additional information about participants as a result of the study.

Building on what is known but bearing in mind scalability, we propose to develop and test a novel intervention to decrease SFA intake. In one group, a brief advice session will provide motivational force using a qualified health professional to explain the importance of SFA intake and the impact this could make to a patient’s cholesterol. But recognising that health professionals may lack sufficient time and training to go beyond general messages about how to reduce SFA, we propose another intervention to provide personalised feedback and self-monitoring of dietary habits, which has further potential to achieve and sustain behaviour change^14^. Therefore, a second group will receive a brief advice session in combination with a personalised report on purchasing behaviours (provided monthly over the 3 months of follow up), to enhance the participants capability to make dietary changes when shopping for food. By drawing on the power of data already collected by supermarkets we are able to automate the process which would otherwise require considerable time from dietitians to deliver. These two groups will be compared to a control group which will just receive their blood test results without any further advice.

We will enrol people with raised LDL cholesterol who are willing to try to change their diet, perhaps to avoid the need for long-term medication. At this stage we will examine the effect of the intervention on saturated fat intake as the primary outcome and, if promising, we will plan for a definitive trial to test the effectiveness of the intervention to reduce LDL cholesterol. This proposed intervention is low cost and could reach large numbers, meaning that it could have a significant population impact and be very cost-effective, even if the effect size is smaller than more intensive interventions. If successful, similar interventions could be offered by supermarkets to all their customers to bring health benefits to the whole population and encouraging supermarkets to play a more proactive role in shaping healthier choices for their customers.

**Aims**

This project aims to develop and test a behavioural intervention to promote reductions in saturated fat (SFA) intake among patients in primary care with raised LDL-cholesterol who are willing to change their diet.

The main hypothesis is that compared to usual care, an intervention involving health professional advice alone and/or in combination with personalised feedback and monitoring on the SFA content of food purchases, will help people reduce dietary SFA intake which, in the longer term, would be expected to lead to reductions in LDL cholesterol.

Specific aims of this research include:

1. To develop an intervention comprising a brief advice session from a qualified health professional to promote healthier eating and reduce saturated fat;
2. In collaboration with a supermarket, to develop a system to provide personalised feedback on the nutritional content of the shopping basket, advice on alternative food options with lower SFA content, and tracking of the SFA content of food purchases over time;
3. To test the effectiveness of brief advice alone and the combined intervention in decreasing SFA intake among patients in primary care with raised LDL cholesterol.

# OBJECTIVES AND OUTCOME MEASURES

**Objectives**

i. Primary objective:

To develop and test the effectiveness of a behavioural intervention to reduce saturated fat (SFA) intake through brief advice from a qualified health professional alone or in combination with feedback on food purchasing behaviours.

ii. Secondary objectives:

To test the effects of the intervention on:

1. Other measures of dietary intake, including changes in mean total energy intake, total fat, total sugars, fibre and salt; and intake of high SFA food groups between baseline and 3 months.
2. Measures of food purchases including changes in mean %SFA from total purchases; energy density, total fat, sugar, fibre and salt from purchases; proportion of food items with low SFA (e.g. products with ≤1.5 grams of SFA per 100 grams of the product); mean total cost of the shopping basket (£) between baseline and 3 months.
3. Biochemical markers of CVD risk, including changes in mean LDL-cholesterol, HDL-cholesterol, total cholesterol and triglycerides; systolic and diastolic blood pressure between baseline and 3 months.
4. Body weight, including changes (absolute (kg) and relative (%)) in body weight between baseline and 3 months.
5. Feasibility of the intervention, including willingness of participants to take part in the study and be randomised to measure recruitment rates; follow-up rates to measure programme attendance and retention; and process measures such as the acceptability of the intervention for participants and health professionals and the uptake of the intervention.
6. Qualitative sub-study outcomes: Themes and sub-themes pertaining to the participants’ (i) knowledge, (ii) perceived barriers, facilitators and actions, (iii) contextual influences, and (iii) value of the healthcare advice provided.

**Outcome measures**

i. Primary outcome: change in mean SFA intake (% from total energy intake) between baseline and 3 months, measured using 2 x 24h dietary recalls twice (once at baseline and once at 3 months) using a validated web based questionnaire. We will measure intake at an individual level. We selected SFA intake as the primary outcome because this is the main target in most dietary interventions that aim to promote a healthier diet to prevent cardiovascular disease. Evidence from recent randomised trials in populations with high CVD risk showed absolute changes in %SFA intakes of around 4-5% when participants were provided with the appropriate food swaps^6 7^.

ii. Secondary and non-efficacy outcomes:

We will also examine changes in food purchasing patterns, including changes in mean %SFA from total purchases; energy density, total fat, sugar, fibre and salt from purchases; proportion of food items with low SFA (e.g. products with ≤1.5 grams of SFA per 100 grams of the product); mean total cost of the shopping basket (£) between baseline and 3 months. This is objective information collected through the storecard data, but available only at a household level. However, measures of the nutrients from the storecard data are expected to be highly correlated with nutrient intakes as captured by the dietary recalls but not perfectly if some participants buy food for themselves and different food for the rest of their household (i.e. only one in the household could be on a diet).

We will explore changes in other dietary intake measures using the same dietary instruments as for the main outcome, including changes in mean total energy intake, total fat, total sugar, fibre and salt, as well as changes in the intake of high SFA food groups between baseline and 3 months. Since the intervention will propose specific healthier swaps to decrease total SFA intake, changes in some of these other nutrients and food groups can also be expected, particularly to energy intake and total fat, or there may be compensatory increases in other nutrients such as sugar.

Changes in the biochemical markers of CVD risk will be also examined, including LDL-cholesterol, HDL-cholesterol, total cholesterol, non-HDL cholesterol, total cholesterol/HDL ratio, triglycerides, systolic and diastolic blood pressure between baseline and 3 months. We selected these biomarkers as they are the prime targets for CVD risk reduction and have improved in previous interventions that provided appropriate food swaps to reduce SFA intake^6 7^. A recent systematic review and meta-analysis found that interventions to reduce SFA intake compared to usual diets resulted in a significant reduction in LDL cholesterol of 0.19 mmol/L [-0.33,-0.05] and 17% reduction in CVD risk^3^.

Changes in body weight (absolute (kg) and relative (%)) will be examined between baseline and 3 months. Although the intervention will only suggest food swaps with lower SFA content, many of these foods are high in energy density and swapping to lower fat intake generally reduces energy density and total energy intake. Hence it is expected that participants in the active intervention arms will decrease their total energy intake and small changes in body weight could be observed as has happened in other behavioural interventions targeting the nutritional quality of the diet in patients with high CVD risk^7^.

We will also assess key elements of feasibility and process measures. These include willingness of participants to take part in the study and be randomised, which will help determine recruitment rates; programme attendance and retention, which will help determine follow-up rates. Finally, we will measure the acceptability of the intervention for participants and health professionals, and process measures will be collected using questionnaires before, and after the intervention period. These include questions to understand if the given information (provided by the BHF leaflet and the purchasing reports) was helpful and clear for the participants and improved their knowledge and motivation to change; if the purchasing report was helpful to them in subsequent shopping episodes and to track their progress; if the report was easy to understand and provided acceptable alternatives with lower SFA; if the frequency of the purchasing reports was adequate; if the purchasing report enhanced their motivation to select items with less SFA, and if the perceived cost of their shopping is unchanged after the intervention. The questionnaire will also assess attitudes towards diagnosis and treatment of dyslipidaemia and cardiovascular disease, and the value of their health care provider offering support to change their diet. Furthermore, uptake of the intervention will be objectively measured by using information on participants’ purchases before and after the intervention to understand if the suggested swaps by the BHF leaflet and/or the purchasing report were accepted and people truly changed their shopping behaviours. Finally, we will also record health professionals’ views and feelings about delivering the brief advice session to improve diet and decrease SFA intake for the participants in the study.

Qualitative study: *A priori* hypotheses and/or outcome measures are not specified. Rather, a deductive thematic analysis approach will draw out themes and sub-themes pertaining to the participants’ (i) knowledge and health values about SFA (ii) perceived barriers and facilitators and actions, (iii) contextual influences that may have affected the overall result, and (iii) value of the healthcare advice provided to motivate and support individuals to change their food purchasing behaviour.

| **Objectives** | **Outcome Measures** | **Timepoints of evaluation of this outcome measure** |
| --- | --- | --- |
| **Primary Objective**  To test a behavioural intervention to promote reductions in saturated fat (SFA) intake through brief advice from a qualified health professional alone or in combination with feedback on food purchasing behaviours | Change in SFA intake, measured using 2 x 24h dietary recalls using the Web-Q instrument. | Mean % SFA intake at baseline and 3 months. |
| **Secondary Outcomes**  1. Purchasing patterns  2. Biochemical markers of CVD risk  3. Food group patterns | 1. Changes in SFA from total purchases; proportion of food items with low SFA (e.g. products with ≤1.5 grams of SFA per 100 grams of the product);  2. Changes in LDL-cholesterol, HDL-cholesterol, total cholesterol and triglycerides;  3. Changes in the intake of high SFA food groups using 2 x 24h dietary recalls. | 1. Mean %SFA from total purchases; proportion of food items with low SFA at baseline and 3 months.  2. Mean LDL-cholesterol, HDL-cholesterol, total cholesterol, non-HDL cholesterol, total cholesterol/HDL ratio and triglycerides at baseline and 3 months.  3. Mean intake (g, kcal) of high SFA foods at baseline and 3 months |
| **Non-efficacy Outcomes**  1. Intake of other nutrients  2. Other purchasing patterns  3. Blood pressure  4. Body weight | 1. Changes in energy intake, total fat, total sugars, fibre and salt using 2 x 24h dietary recalls.  2. Changes in energy density, total fat, sugar, fibre and salt from purchases; mean total cost of the shopping basket (£).  3. Changes in systolic and diastolic blood pressure.  4. Changes (absolute (kg) and relative (%)) in body weight. | 1. Mean total energy intake, total fat, total sugars, fibre and salt at baseline and 3 months.  2. Mean energy density, total fat, sugar, fibre and salt from purchases; and mean total cost of the shopping basket (£) at baseline and 3 months.  3. Mean systolic and diastolic blood pressure at baseline and 3 months.  4. Mean body weight at baseline and 3 months. |
| **5. Feasibility and Process Measures**   - Recruitment rates - Follow-up rates - Acceptability and views of the intervention; and other process measures | - Willingness of participants to take part in the study and be randomised. - Programme attendance and retention. - Acceptability of the intervention for participants and health professionals; uptake of knowledge, motivation and swaps accepted. | - Number of participants who accept the invitation, consent to take part in the study and are randomised at baseline - Number of participants who return for the follow up visit at 3 months - Questionnaires at baseline, 3 months and immediately after the intervention is delivered. Number and types of swaps purchased during the intervention. |
| **Qualitative Sub-study** | To conduct a semi-structured, one-to-one, telephone interview with a sub-sample of the PC-SHOP study participants to explore issues related to food purchasing behaviours, including knowledge, perceived barriers, facilitators and actions, contextual influences, and value of the healthcare advice provided. | Themes and sub-themes pertaining to the participants’ (i) knowledge, (ii) perceived barriers, facilitators and actions, (iii) contextual influences, and (iii) value of the healthcare advice provided. |

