# INTERVENTIONS

The two active interventions will incorporate strategies which use the Behaviour Change Wheel COM-B model as a theoretical framework to guide the choice of behavioural strategies^13 17^. Briefly, the proposed interventions aim to allow participants to develop and sustain the capability, opportunity and motivation to make changes to diet^13^. Psychological capability will be enhanced by educating participants on SFA and health risks as well as information on the most appropriate swaps to decrease their SFA intake. Opportunity will be supported by the shopping report which will highlight the top 3 individual sources of SFA and proposed swaps to those, therefore making healthier choices easier to spot by participants. Motivation will be promoted by the shopping report by allowing participants to track and monitor their progress over time, as well as by the health professional advice which will provide further motivation to attempt the change and facilitate understanding of the value of these changes on health.

Participants will be randomised to one of the three conditions explained below. Participants randomised to receive intervention 1 and 2 which involves a brief advice session, will be asked to consent to have the session audio-recorded to allow for fidelity testing. The purpose of fidelity testing is to determine:

- If the brief advice session in being delivered according to the intended protocol and behavioural theoretical models.

- If number frequency, length and content of the sessions are similar across all participants within each group.

- Compare and identify successful and unsuccessful aspects of the interventions.

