## Intervention 1: Brief advice session

This intervention will be a single one-to-one appointment with the health professional (HP) in which they will receive advice on the importance of dietary change and motivation to reduce SFA based on the British Heart Foundation “*Cut the Saturated Fat*” chart^18 19^, which will be provided as printed educational material.

This session is aimed to inform participants about the benefits of saturated fat reduction and encourage them to attempt it. Dietary advice will be particularly focused on explaining the different sources of fat and the most appropriate changes proposed in the BHF guidance to decrease SFA, primarily by substitution with lower SFA options (e.g. change from regular beef to lean beef); or with mono- and polyunsaturated fat sources (e.g. change from butter to low-fat vegetable spread).

Health professionals will be trained to deliver this session face-to-face during approximately 10min. The structure of the session will be standardised so that it will follow 3 major discussion points. The HP will start by discussing cardiovascular risk with the participant and will provide the participant with the results of the blood tests. The HP will then highlight that diet is a very important modifiable risk factor which can potentially help them decrease this risk by lowering their blood lipids. The second point of discussion will focus on the major sources of SFA in different foods. The HP will carefully explain the educational materials with special emphasis on the major sources of SFA in the UK (dairy, meat and cakes/biscuits). The session will end with a few minutes for questions and final remarks in which the participant can ask any questions in regards to the information provided and the HP will finish the session by emphasising that the proposed changes can achieve very good results in a short time period.

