## Intervention 2: Brief advice session and shopping report

In addition to the brief advice session detailed above, participants in this intervention arm will receive a personalised report with the nutritional composition of foods and beverages purchased from Tesco over the previous 3 months (baseline) and subsequent months (monthly over the 3 months of follow up). This report will include information on total saturated fat (g) and the major food contributors to SFA. Participants will receive monthly reports to allow them to chart their progress in reducing SFA in their grocery purchases. This information will be accompanied by a list with suggestions for one-for-one swaps for foods high in SFA for lower SFA foods to support dietary change.

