## Control group

Participants in the control group (usual care) will be recruited into the study and will be informed of their blood tests by the study team. They will be seen again at 3 months for collecting outcome measures.

Upon completion of the study, all participants including those in the control group will receive a final report with the nutritional information of their purchases over the 3 months during which they were enrolled in the intervention. The control group will also be sent the BHF booklet.

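### Swap uptake is read from before-and-after purchases with no reference rate, so background buying, and in arm 2 regression to the mean, can be counted as uptake (minor: process measure only)

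*Protocol*

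**What the plan says.** Under Outcome measures in Section 5, the protocol says that uptake will be measured objectively from participants' "purchases before and after the intervention to understand if the suggested swaps by the BHF leaflet and/or the purchasing report were accepted". The same sentence gives the inference to be drawn: whether the swaps "were accepted and people truly changed their shopping behaviours". In the objectives table of that section, uptake sits under feasibility and process measures, and its operational form is "Number and types of swaps purchased during the intervention". Neither place names a comparison arm or a background purchase rate.

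The two kinds of swap are chosen differently. Section 9 describes a "shopping report which will highlight the top 3 individual sources of SFA and proposed swaps to those". Section 9.2 gives this report to arm 2 only, starting from the previous 3 months of purchases and continuing monthly. The leaflet swaps used in both active arms are general advice: Section 9.1 has the health professional explain "the most appropriate changes proposed in the BHF guidance to decrease SFA".

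Purchase data are not confined to arm 2. Section 8.3 requires storecard details before anyone is randomised, and Section 9.3 says that "all participants including those in the control group will receive a final report with the nutritional information of their purchases". The regression in Sections 11.1 and 11.3 is stated for primary and secondary outcomes. Process measures are not named there, apart from bar charts of the acceptability questionnaire.

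**The concern.** A count of swap products bought during the intervention mixes two things: purchases prompted by the report or leaflet, and purchases that ordinary brand switching, promotions or season would have produced anyway. Without a rate in people who were not given the list, the two cannot be separated.

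The before-and-after reading adds a second problem in arm 2. Items picked because they ranked highest in one window tend to fall back in the next, with no change in behaviour.

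The study is meant to inform a definitive trial. Suppose intake did not change but apparent uptake was high. The natural reading would be that people adopted the swaps and the swaps did not work, when the swaps might hardly have been adopted at all.

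**Working it through.** The protocol states no expected uptake, so there is no figure to reproduce. The checks below ask whether the two mechanisms operate when the intervention does nothing, and what a between-arm comparison could detect.

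**Inputs from the protocol**
- Baseline window of 3 months, follow-up of 3 months, top 3 items chosen on baseline (Sections 9 and 9.2).
- Arms of 16, 48 and 48, with 10% attrition (Section 11.2).
- A 4-week baseline if the till-receipt contingency is used (Section 8.6).

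**Assumptions (not in the protocol).** Purchases of each item are Poisson. Rates vary between items as a gamma distribution with mean m purchases per 3-month window (1, 3 or 8) and coefficient of variation CV (0.5 or 1.0). There are 40 or 100 items per household, SFA per purchase is lognormal, and 4,000 households are simulated with the same rates in both windows, so nothing changes.

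**1. Background purchasing, the mechanism that affects the stated count.** Take a product not bought at baseline. With k = 1/CV² and b = k/m, the chance that it is bought at follow-up with no intervention is

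P = 1 − [(b + 1)/(b + 2)]^k

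- CV 1.0, m = 1: k = 1, b = 1, P = 1 − 2/3 = 0.33.
- CV 1.0, m = 8: k = 1, b = 0.125, P = 1 − 1.125/2.125 = 0.47.
- CV 0.5, m = 1: k = 4, b = 4, P = 1 − (5/6)^4 = 0.52.
- CV 0.5, m = 8: k = 4, b = 0.5, P = 1 − (1.5/2.5)^4 = 0.87.

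The simulation gave the same values, a range of 0.33 to 0.87. This treats a swap product as bought at rates like any other item. A product that the household rarely buys would have a lower value.

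**2. Regression to the mean in the arm 2 top 3.** Change in SFA from the baseline top 3 items, with no effect:

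| Mean purchases per item per window | Fall in top-3 SFA |
| --- | --- |
| 8 | 6% to 14% |
| 3 | 15% to 29% |
| 1 | 34% to 51% |

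Total SFA purchased changed by 0.3% or less in every setting. So the artefact comes from selecting the items, and whole-basket measures do not carry it.

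A second set of assumptions used 15 to 30 SFA-containing products, 0.3 packs per week each, and gamma shape 0.5 to 2. It gave falls of 6% to 17% with a 13-week baseline and 19% to 38% with a 4-week baseline.

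**3. What a between-arm comparison could detect.** After 10% attrition, 16 × 0.9 = 14.4 and 48 × 0.9 = 43.2. The detectable standardised difference at two-sided 5% is (1.960 + z_power) × √(1/n1 + 1/n2), with z_power = 0.842 for 80% power and 1.282 for 90%.

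- Arm 2 vs arm 1: √(2/43.2) = 0.215, so 2.802 × 0.215 = 0.60 SD at 80% power and 3.242 × 0.215 = 0.70 SD at 90%.
- Active arm vs control: √(1/14.4 + 1/43.2) = 0.304, so 2.802 × 0.304 = 0.85 SD at 80% power and 3.242 × 0.304 = 0.99 SD at 90%.

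**The case against.** Much of the case on the other side stands.

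- **Other objective evidence exists.** A reader might infer that this is the only objective check on whether the report works. It is not. Change in %SFA of total purchases and the share of low-SFA items are secondary outcomes, drawn from storecard data and analysed by baseline-adjusted regression between randomised arms. They do not, however, show whether the suggested swaps were the route of any change, which is what the uptake measure is for.
- **The simulated fall is not bias in the count.** The 6% to 51% concerns SFA from the top 3 items. A fall there does not in itself add swap purchases. It bears on the before-and-after reading, while the count is exposed to background buying. Both figures rest on assumed purchase rates.
- **Selection is confined to arm 2.** Leaflet swaps are not chosen from a person's baseline, so regression to the mean does not reach them through selection.
- **It is not certain to look like uptake.** A 3-month baseline damps the effect for items bought often, and about 10 months of recruitment partly averages out season.
- **Silence on arms, and the analysis plan.** The protocol words other outcomes as change from baseline without naming arms, and it promises a detailed analysis plan, which is not at hand and may define a comparison. But for primary and secondary outcomes Section 11 supplies the arms. For swap uptake nothing in the protocol does, and Section 5 itself attaches the claim of real behaviour change. A comparison in the analysis plan would also need swap lists for people who never received a report, and the protocol does not provide for these. The final report in Section 9.3 covers the 3 months of enrolment, so it does not supply baseline swap lists.

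**Conclusion.** The concern holds as a minor point. As worded, the uptake measure has no reference rate and cannot support the inference that people truly changed their shopping. Background buying can be counted as uptake for both kinds of swap, and a before-and-after fall in the arm 2 target items is open to regression to the mean as well. The direction does not depend on the assumptions, but the size does: it turns on purchase frequencies that the protocol does not give, so the simulated ranges are illustrations and not estimates for this trial.

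A reader might go further and doubt the trial's conclusions on purchasing. The documents do not support that: the randomised comparison of whole-basket outcomes is untouched by the selection of items.

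**What to change.** - Run the same top-3 and swap algorithm on baseline purchases for every randomised participant. Store the lists unsent for arm 1 and control.
- Count purchases of listed swaps, and of BHF leaflet swaps, over the same follow-up window in all three arms.
- In the objectives table, define uptake as the between-arm difference with a 95% confidence interval. For report swaps the main contrast is arm 2 vs arm 1. The contrast with control can be shown, but it is imprecise with about 14 controls after attrition.
- Keep within-arm counts as descriptive only, and limit the claim of changed behaviour in Section 5 to the between-arm result.

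The cost is protocol wording and some programming. Baseline and follow-up purchases are already needed in every arm for the secondary outcomes, and Section 4 intends report generation to be automated. If the till-receipt contingency in Section 8.6 is used, coding receipts and building lists by hand for arm 1 and control is real extra work.
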